### Secondary outcomes

The secondary outcomes of the trial are: 1) Effectiveness of SMATH^® ^determined by evaluating self perceived physical function comparing RMDQ scores between end of treatment and baseline. 2) Pain perception change from baseline (T2) to end-treatment (T4), evaluated by VAS scores. 3) Quality of life at different steps of the study (T2 and T4), evaluated by EQ-5D scores (QALY). 4) Verified general feasibility of the medical device compared to sham therapy in terms of methodology, sample size, and drop-out rate, among other measures, to constitute a real pilot study and act as a possible reference for future generations of RCTs involving the medical device, conforming to the evidence-based medicine (EBM) criteria for LBP therapy [13] according to the CONSORT statement based on new methodological evidence and to the International Placebo Symposium Working Group recommendations [19].

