**Methods/design:**

This paper describes the protocol for a double-blinded, sham-controlled, randomized, single-center short term clinical trial in patients with non-specific sub-acute and chronic LBP aged 18 to 70 years. The primary outcome will be the effectiveness of SMATH^® ^versus sham therapy (medical device without active principles) determined by evaluating self perceived physical function with Roland Morris Disability Questionnaire (RMDQ) scores after 4 weeks of treatment (end of treatment). Major secondary outcome will be effectiveness of SMATH^® ^determined by evaluating self perceived physical function comparing RMDQ scores between end of treatment and baseline. The trial part of the study will take 7 months while observational follow-up will take 11 months. The sample size will be 72 participants (36 for each arm). The project has been approved by the Ethical Committee of Cremona Hospital, Italy on 29 November 2010.

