LBP has been difficult to treat solely using medical interventions due to the complex interplay of biological, psychological, and social factors in its onset and persistence. LBP is usually a benign and self-limiting condition, but many patients look for some type of therapy to relieve their symptoms and provide hope for a cure. For this reason, more than 50 potential therapies promise to relieve the pain [2,9], lessen the suffering, and offer a cure for this problem. However, sound evidence exists for a small number of these therapies [9]. For the interventions with multiple reviews, conflicting conclusions have been reached about effectiveness due to the heterogeneity and poor quality of the trials, but there are more qualitative systematic reviews than meta-analyses, and two-thirds of systematic review authors emphasize that more high quality trials are needed [10]. Despite advances in knowledge, technology, and procedures, no medical treatment has been demonstrated to consistently and completely alleviate LBP. Clinical evidence for the majority of treatments used in LBP therapy is also inconsistent. However, moderate evidence exists for interdisciplinary rehabilitation, exercise, acupuncture, spinal manipulation, and cognitive behavioral therapy for sub-acute and chronic LBP [5,11]. In particular, multidisciplinary interventions seem to be the most promising approach for patients with sub-acute and chronic LBP [12]. Intensive multidisciplinary biopsychosocial rehabilitation with a functional restoration approach has been shown to reduce pain and improve function in patients with chronic LBP [13]. In addition, empirical evidence has shown the sort of information and advice that should be given to patients with back pain, confirming that such information and advice may be a potent element of the health care intervention [14]. Soft-tissue massage is thought to improve physiological and clinical outcomes by offering symptomatic pain relief through physical and mental relaxation and increasing the pain threshold via the release of endorphins [2,15]. The gate-control theory predicts that massaging a particular area stimulates large diameter nerve fibers. These fibers have an inhibitory electrical input to T cells, which are the first cells to project into the central nervous system within the spinal cord [2]. T-cell activity is likely depressed, whereas small diameter nerve fibers (nociceptive fibers) have an excitatory input, and pain relief follows [16]. Massage therapy may provide benefits by shifting the autonomic nervous system from a state of sympathetic response to a state of parasympathetic response. Massage is similar or superior to other conservative therapies, such as exercises, mobilization, relaxation, physical therapy, acupuncture, and self-care education [2]. Massage is beneficial for patients with sub-acute and chronic nonspecific LBP in terms of improving symptoms and function, but the benefits of massage increase when combined with exercises and education [2]. Massage has powerful analgesic effects if applied to acupuncture points, a technique known as "acupressure" [2]. Two studies that compared massage to inert treatment (sham therapies) showed that massage is superior for pain and function in both short and long-term follow-up [17,18]. No serious adverse events were reported by any patient in the studies reviewed [2]. Massage alone is unlikely to be cost-effective [5]. Focusing on high-quality randomized controlled trials (RCTs) with a sufficient sample size to draw firm conclusions is particularly recommended for future research involving LBP therapies [12].

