
The cost/effectiveness ratio for the SMATH^® ^system may also be interesting and could play an important role in the Italian NHS strategy for LBP interventions. An HTA procedure has already been launched in Italy for this new therapy. Like all new technologies and interventions, the clinical effectiveness of the SMATH^® ^system has to be proven by clinical studies in a PRM context. Compared to other medical specialties, PRM has not yet received the recognition deserved from clinicians and researchers in the scientific community, especially for medical devices [19]. We think this unfavorable scenario is due to several reasons, one of which is the lack of high-quality clinical trials in the PRM field. Conducting double-blind placebo-controlled trials in the specialty is difficult; the majority of studies in PRM are practically based on clinical observation, uncontrolled observational studies, or clinical trials comparing two different active therapies. Consequently, these studies are not suitable for providing sufficient proof of efficacy for these therapeutic modalities. The only scientifically recognized way to achieve this goal is to design and manage high-quality double-blind placebo-controlled trials. Sham treatment groups in clinical trials are essential for improving the level of evidence-based practice in PRM. This trial was conceived to reduce the lack of evidence and quality for LBP therapy. No major and minor adverse events or adverse effects have been observed during the use SMATH^® ^on patients with LBP. The SMATH^® ^system has the CE mark as it has passed all tests concerning safety for the patient, operators, and environment. For this reason, no adverse events are expected during this clinical study. However, if adverse events occur, they will be reported to the regulatory authority and ethics committee in accordance with applicable regulations. Trial results will be used to inform HTA procedure already involving SMATH^® ^therapy for health care policies regarding the treatment of LBP in Italy.

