### Primary outcome

The primary outcome of the trial is represented by the clinical effectiveness of the SMATH^® ^system versus sham therapy after 4 weeks of treatment in patients with sub-acute and chronic non-specific LBP, determined by evaluating self perceived physical function with RMDQ scores. The status of physical function in participants treated with SMATH^® ^interventions will be compared with the status achieved in participants in the sham control arm at the end of treatment (T4) [12].

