### Assessment of outcomes

Four steps of participant examination are planned in this RCT (T1, T2, T3, and T4); during which, general clinical data will be collected about the persistence of LBP symptoms, previous treatment, morphological data, patient activity, blood chemistry tests, anamnesis, and eventual clinically important imaging investigations that were recently done. The effectiveness of SMATH^® ^versus sham will be determined by evaluating self-perceived physical function with RMDQ scores at T4. The secondary outcome of SMATH^® ^therapy effectiveness will be determined by evaluating improvements in patients' motion functionality between T2 and T4 using RMDQ scores. The evolution of pain perception during the study will be measured by VAS scores submitted by the participants at T2, T3, and T4. Quality of life for participants will be estimated by the comparing the EQ-5D questionnaires submitted at the beginning and end of treatment (T2 and T4). During the observational follow-up period all participants will be examined at TF1, TF2, TF3, TF4, and TF5 for general patient status: anamnesis, blood pressure, heart rate in beats per minute, and morphological variables (height, weight, Body Mass Index [BMI]). The RMDQ and VAS questionnaires will be given on the participants at TF1, TF2, TF3, TF4, and TF5, and EQ-5D will be given at TF1, TF2, and TF5. All of the data collected during the study and follow-up will be reported to the CRF.

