### Statistics and quality

The accuracy and completeness of the collected and registered data will be checked daily by clinical investigators to provide a suitable level of quality for the study. The external monitor will be responsible for arranging random periodic tests of quality throughout the study. In particular, controls will involve the quality and completeness of the CRFs, the treatment execution modalities, the drop-out rate, and correct respect of enrollment criteria application. Data analysis will be conducted using IBMSPSS 19 [21,22]. The morphological and clinical status of participants will be analyzed statistically. Motion functionality, level of pain perception, and quality of life will be evaluated through statistical analysis of the questionnaire scores. Short-term results will be evaluated to elaborate VAS and RMDQ scores, and medium and long-term results will be evaluated by EQ-5D scores, which will also be used to calculate the QALY and incremental cost effectiveness ratio (ICER) index [5,22], which is the most used and suitable index for analyzing the cost/effectiveness of PRM therapies [5]. Pain perception measured by VAS in the different phases and its severity analysis will be evaluated by analysis of variance using SPSS 19. Event incidence (SMATH^® ^versus sham) will be estimated using Kaplan-Meier curves, which will be compared using the log-rank test. Multivariable analysis will be performed using the Cox model.

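### The first secondary outcome calls a T2-to-T4 RMDQ change the effectiveness of SMATH without naming the sham comparison

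*Protocol article*

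**What the plan says.** Three places in the Protocol article define this outcome.

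- **Abstract, Methods/design:** "Major secondary outcome will be effectiveness of SMATH", assessed on end-of-treatment against baseline RMDQ scores.
- **Secondary outcomes, item 1:** effectiveness is "determined by evaluating self perceived physical function comparing RMDQ scores between end of treatment and baseline".
- **Assessment of outcomes:** effectiveness of the therapy "will be determined by evaluating improvements in patients' motion functionality between T2 and T4 using RMDQ scores".

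None of them mentions sham. The primary outcome is worded differently: under Primary outcome, the status of SMATH participants "will be compared with the status achieved in participants in the sham control arm at the end of treatment (T4". The Abstract and Assessment of outcomes also put the primary as SMATH against sham, in the sentence just before the secondary outcome. Item 4 of the secondary outcomes (feasibility) names sham as well.

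Statistics and quality says that questionnaire scores will be analysed statistically. It names no between-arm test of RMDQ change.

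**The concern.** A change within one arm contains everything that happens to participants over four weeks, not only the device effect. The protocol itself gives reasons to expect some improvement without one:

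- Background states that "LBP is usually a benign and self-limiting condition".
- Interventions for each group accepts that the sham may produce a placebo effect.
- The same section gives the educational booklet to every enrolled participant.

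Trial Rationale says of observational, uncontrolled and active-against-active studies in this field that "these studies are not suitable for providing sufficient proof of efficacy for these therapeutic modalities", and presents the sham-controlled design as the remedy. An effectiveness outcome read before-after brings the criticised design back inside the trial. At stake is a report in which the sham comparison is null while a prominent secondary result is still labelled effectiveness. Trial Rationale adds that the trial's results will inform an Italian health technology assessment.

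**Working it through.** **1. The plan's own figure.** The protocol gives no figure for this outcome. Its sample size rests on a between-arm difference and reproduces. With P1 = 0.50, P2 = 0.10, two-sided alpha 0.05 (sidedness is not stated) and 90% power:

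n = [1.960 × √(2 × 0.30 × 0.70) + 1.2816 × √(0.50 × 0.50 + 0.10 × 0.90)]² / 0.40² = (1.270 + 0.747)² / 0.16 ≈ 25.4, so 26 per arm.

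The stated drop-out factor gives 26 × 1/(0.85)² = 35.99, so 36 per arm. This is not in dispute.

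**2. Inputs for the illustration.**

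| Input | Value | Source |
|---|---|---|
| RMDQ SD | 3.0 | Trial Rationale, safety study of 46 patients: 3.04 at baseline, 2.99 at 3 months |
| Evaluable in SMATH arm | 30 | 36 × 0.85 = 30.6, rounded down |
| T2–T4 correlation r | 0.5 (range 0.3 to 0.7) | Assumed |
| Non-specific fall d, same in both arms | 0, 0.5, 1, 2 points | Assumed |
| Test | Within-arm paired t-test, two-sided 0.05 | Assumed; the protocol names none |
| Device effect | 0 | Set, to see what the outcome reports for an inert device |

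**3. Smallest significant fall.** SD of change = 3.0 × √(2(1 − r)) = 3.0 at r = 0.5. Critical mean fall = 2.045 × 3.0/√30 = 1.12 points.

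**4. Chance of a significant fall.** This is the power of the paired t-test from the noncentral t distribution with 29 degrees of freedom and noncentrality d/(3.0/√30) = d/0.548.

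| Shared fall d | Noncentrality | Within-arm test significant | Between-arm test of change significant |
|---|---|---|---|
| 0 | 0 | 5% | 5% |
| 0.5 | 0.91 | 14% | 5% |
| 1 | 1.83 | 42% | 5% |
| 2 | 3.65 | 94% | 5% |

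The last column is 5% throughout because a fall shared by both arms cancels in the difference. A simulation with 30 per arm gave 4.9% to 5.1% in that column.

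**5. Sensitivity at d = 2.** With 30 evaluable, the within-arm figure is 85% at r = 0.3, 99.5% at r = 0.7 and 70% at r = 0. With all 36 evaluable and r = 0.5 it is 97%. If the SD of change were 6, it would be 42% with 30 and 49% with 36.

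**The case against.** The strongest reply is that nothing excludes the sham arm. The wording in Assessment of outcomes ("improvements in patients' motion functionality between T2 and T4 using RMDQ scores") speaks of patients generally, and a change score in a two-arm trial is commonly compared between arms, with the contrast left to an analysis plan. That reading is possible but weaker: the authors name sham for the primary outcome and for feasibility, and omit it here in an adjacent sentence. If they did mean a between-arm contrast, all three definitions still misstate it.

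The reply also limits the point. A reader might infer several stronger things that the documents do not support:

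- **That the outcome would show effectiveness whatever happens.** With no non-specific fall the within-arm error rate is 5%, and at 0.5 points only 14%. The self-limiting remark concerns low back pain in general, whereas the trial enrols sub-acute and chronic cases, so it does not fix a four-week fall.
- **That selection on RMDQ of at least 4 at T2 drives the change through regression to the mean.** Assume normality and the safety study's baseline (10.96, SD 3.04). The cut-off then lies (10.96 − 4)/3.04 = 2.29 SD below the mean, removes about 1% and moves the mean by about 0.09 points. At r = 0.5 the regression is about 0.04 points, which is negligible.
- **That VAS and EQ-5D share the fault.** Items 2 and 3 give variables and times and do not claim effectiveness of SMATH. The VAS sentence ("Pain perception measured by VAS in the different phases and its severity analysis will be evaluated by analysis of variance") does not say that arm is left out of the model. EQ-5D also feeds an incremental cost-effectiveness ratio, which needs a comparator.
- **That the trial's main conclusion is compromised.** The primary outcome is an explicit sham comparison on the same instrument, so a null result would stand beside any within-arm change. The health technology assessment is to use the trial's results, which include that comparison.

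**Conclusion.** The point holds for secondary outcome 1 only and should be fixed. As worded, it attaches effectiveness to an RMDQ change with no stated control, and an analysis that followed the wording would credit the device with any non-specific improvement. For an inert device, the chance of a significant within-arm fall runs from 5% with no shared fall to 94% with a 2-point fall (85% to 99.5% for r from 0.3 to 0.7), against 5% between arms. These figures show the mechanism and do not predict the result, because they rest on the assumed test, fall and correlation and on SDs borrowed from a 3-month uncontrolled study. The fault lies in what three sections state, so it is not a matter of detail left to an analysis plan.

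**What to change.** In the Abstract, in item 1 of Secondary outcomes and in Assessment of outcomes, define the outcome as the SMATH-minus-sham difference in RMDQ change from T2 to T4, adjusted for the T2 score (for example by ANCOVA), with a 95% CI. Report within-arm changes descriptively for both arms, without the word effectiveness.

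The VAS and EQ-5D outcomes may be worded the same way for consistency, but the text does not require it.

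The cost is a wording change in three places. Visits, questionnaires, randomisation and the 36 per arm stay as they are. What is given up is a result that would tend to look favourable whenever participants improve for any reason.

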### Observational follow-up and duration of the study

Observational follow-up will start at TF1 (T4) and cover 11 months. During this period, all of the participants will come to the treatment centre to attend clinic visits one month after TF1 (TF2), 3 months after TF2 (TF3), 3 months after TF3 (TF4), and 4 months after TF4 (TF5). Figure 2 shows the design of the observational follow-up period. The estimated study duration for enrollment, execution and observational follow-up will be 18 months.

### Assessment of outcomes

Four steps of participant examination are planned in this RCT (T1, T2, T3, and T4); during which, general clinical data will be collected about the persistence of LBP symptoms, previous treatment, morphological data, patient activity, blood chemistry tests, anamnesis, and eventual clinically important imaging investigations that were recently done. The effectiveness of SMATH^® ^versus sham will be determined by evaluating self-perceived physical function with RMDQ scores at T4. The secondary outcome of SMATH^® ^therapy effectiveness will be determined by evaluating improvements in patients' motion functionality between T2 and T4 using RMDQ scores. The evolution of pain perception during the study will be measured by VAS scores submitted by the participants at T2, T3, and T4. Quality of life for participants will be estimated by the comparing the EQ-5D questionnaires submitted at the beginning and end of treatment (T2 and T4). During the observational follow-up period all participants will be examined at TF1, TF2, TF3, TF4, and TF5 for general patient status: anamnesis, blood pressure, heart rate in beats per minute, and morphological variables (height, weight, Body Mass Index [BMI]). The RMDQ and VAS questionnaires will be given on the participants at TF1, TF2, TF3, TF4, and TF5, and EQ-5D will be given at TF1, TF2, and TF5. All of the data collected during the study and follow-up will be reported to the CRF.

### Sample size calculation

Due to the difficulty of finding solid references in the literature regarding the probability of success for different arms of RCTs comparing therapy with medical devices versus sham therapy [19], some basic statistical assumptions have been made in regards to the level of inhibition technically introduced into the SMATH^® ^active principles to obtain a sham device. The therapeutic effect induced by the sham device has been estimated to be 10% of the effect induced by the SMATH^® ^system. Consequently, the probability of SMATH^® ^therapy success has been fixed at 50% (P_1_) [2], whereas a probability of 10% (P_2_) has been fixed for success with sham therapy. Thus, the success difference between the two study arms (P_1 _- P_2_) is 40%. This important delta has been fixed to be statistically significant also in the case of unexpected placebo effect of sham. The false-positive risk factor α (type I error rate) has been fixed at 0.05 (5%). The probability of discovering a difference between the two study arms has been fixed at 90% (study's power). Based on the study's power, (1 - β) = 0.9, the false-negative risk factor rate β is 0.1 (10%). The value of the function *f *(α, β) was calculated by Geigy's tables [23]. Thus, the sample size in each arm of the study (n) should be n = 26. Drop-out has been considered to prevent having an insufficient sample at the end of the study due at the high risk of drop-out of participants in sham arm. A drop-out rate of 15% (0.15) has been estimated based on the literature concerning RCT versus sham in PRM [19]. The sample adjusting factor μ was calculated using the formula μ = 1/(1 - R)^2 ^[24-26], where R represents the drop-out rate. Therefore, μ = 1/(1 - 0.15)^2 ^= 1.3841, and the sample size after correcting for drop-out will be:n# = nμ = 36. The sample of each group will be 36 participants for a total study group of 72 subjects.

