During the first and second week (from T2 to T3), 4 sessions will be done per week, whereas 3 sessions per week will be planned for the third and fourth week (from T3 to T4). The SMATH^® ^system will be set-up with treatment variables (warm-up time, automatic treatment program, active element temperature, infrared insertion) conforming to the scheduled treatment data sheet delivered to the technician after randomization. Sham therapy will be implemented using a dedicated SMATH^® ^device. This medical device, which was conceived and manufactured exclusively for this clinical study, has the same external look and design of the SMATH^® ^device. The active principles (thermomechanic and infrared energy release) have been fully blocked in the sham device, but the participants' perceptions will be more or less the same (warm, vibration, noise). The engineering department has made important efforts to create a device with the appearance of the active machine, inducing feelings similar to those of the real device [19]. This effect has been obtained by applying some technical solutions without releasing any active energy. Thermal perception is generated using special lamps with different wavelengths than the real SMATH^® ^device with 90% less thermal power (just to induce the feeling of heat). Infrared emission has been removed, as well as the active rollers that release mechanical energy to the back and legs, replaced by an inert, flat wood plate. The sham device will be set-up with the same treatment variables as the SMATH^® ^device. The noise and vibration generated by the sham device will be the same as that of the SMATH^® ^system because the devices have the same mechanical configuration, including the same motor and transmission equipment, operating in the same mode. Despite this similarity, a therapeutic placebo effect could be introduced by the sham device. This risk has been considered and accepted as a natural risk of the RCT with a sham control.

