Participants assigned to the sham therapy arm will receive the same treatment module scheduled for the active SMATH^® ^arm (14 sessions in four weeks from T2 to T4). The participants in the sham arm will also receive the educational booklet. The SMATH^® ^and sham devices are located inside two different therapy boxes and treatment will be given at separate times to prevent contact between participants in the different treatment arms. The operators managing treatments will be the same for the SMATH^® ^and sham devices, and they have been trained to answer the participants' questions about the procedures. The same operators will also be trained and educated in keeping participants in the study, avoiding an increased drop-out rate. The main features of the SMATH^® ^system and sham version are presented in Figures 4 and 5, respectively.

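### The 40-point delta does not protect the trial against a sham placebo response: 90% power holds only up to about 12–15% sham success

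*Protocol article*

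**What the plan says.** All of the planning figures are in the Sample size calculation section of the protocol article.

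- Premise for the sham arm, based on how far the device's active principles were technically inhibited: "The therapeutic effect induced by the sham device has been estimated to be 10% of the effect induced by the" SMATH system.
- As a stated consequence, success is set at 50% for SMATH (P1, with a literature reference) and 10% for sham (P2, with none), a difference of 40 percentage points.
- Assurance about that difference: "This important delta has been fixed to be statistically significant also in the case of unexpected placebo effect of sham".
- The type I error rate is 5%, sidedness not stated. On power: "The probability of discovering a difference between the two study arms has been fixed at 90"%.
- The result is 26 per arm, inflated by 1/(1 − 0.15)² to 36 per arm, 72 in total. No other sham rate is considered.

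Elsewhere the article gives reasons why patients in the sham arm might improve. The Background says "LBP is usually a benign and self-limiting condition". The section on Interventions for each group concedes that "a therapeutic placebo effect could be introduced by the sham device", accepts this as a risk of the design, and adds: "The participants in the sham arm will also receive the educational booklet". The primary outcome is self-reported.

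**The concern.** The assurance runs the wrong way. The required sample falls roughly with the square of the assumed difference, so planning for a large difference yields a small trial. A small trial is the one that suffers most when the sham arm does better than planned. Nothing in the calculation provides for a sham rate above 10%, apart from whatever drop-out allowance happens not to be used.

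The derivation of the 10% is also not shown. An effect that is one tenth of another effect is a relative statement, but it reappears as an absolute success probability of 10%.

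At stake is a statement about the design's robustness that readers will take at face value, including those running the health technology assessment that the article says the results will inform. An analysis plan could not repair this by adding detail, because the article asserts a property that its own figures do not support.

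**Working it through.** **Inputs.** From the Sample size calculation section: P1 = 0.50, P2 = 0.10, α = 0.05, power 0.90, drop-out 15%, 26 then 36 per arm. Assumed here: a two-sided test, and sham rates other than 10%, for which the article gives no figure.

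**1. Reproduce the article's figure.** With the pooled-variance formula and p̄ = (P1 + P2)/2,

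n = [z₀.₉₇₅ √(2p̄(1 − p̄)) + z₀.₉₀ √(P1(1 − P1) + P2(1 − P2))]² / (P1 − P2)²

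= [1.960 × √0.42 + 1.282 × √0.34]² / 0.16 = 25.4, so 26 per arm.

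Drop-out: 26/0.85² = 35.99, so 36. Both figures agree with the article. Expected completers are 36 × 0.85 = 30.6; 30 is used below.

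The choice of two-sided rests on this match. A one-sided test gives 21 without and 26 with a continuity correction, so the match is good evidence but not proof.

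**2. Power when only the sham rate changes.** The same formula solved for power, with P1 held at 0.50:

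power = Φ{ [|P1 − P2| √n − 1.960 √(2p̄(1 − p̄))] / √(P1(1 − P1) + P2(1 − P2)) }

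Example, sham 30%, n = 30: (0.2 × √30 − 1.960 × √0.48)/√0.46 = (1.095 − 1.358)/0.678 = −0.387, so power is 35%.

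| Sham success (above 10%: assumed) | 30 per arm | 36 per arm | n per arm needed for 90% |
|---|---|---|---|
| 10% | 94% | 97% | 26 |
| 15% | 84% | 90% | 36 |
| 20% | 69% | 77% | 52 |
| 30% | 35% | 41% | 124 |
| 40% | 12% | 13% | 519 |

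Exact enumeration of the chi-square test agrees closely: 69% and 79% at 20% sham, 35% and 41% at 30%. Fisher's exact test is lower (26% and 31% at 30% sham). A one-sided 5% test gives 47% with 30 per arm at 30% sham, still far below 90%.

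**3. Where the stated power is lost.** Setting power to 90% and solving for the sham rate gives 10.3% with 26 per arm, 12.5% with 30 and 15.2% with 36. For 80% power the limits are 16.6% with 30 and 19.1% with 36.

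**4. If placebo response lifts both arms equally.** The 40-point difference then survives. Power with 30 and 36 per arm is 91% and 95% at 60% versus 20%, and 89% and 94% at 70% versus 30%.

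**5. The step to P2.** Read directly, 0.10 × 50% = 5%. For 50% versus 5% the formula in step 1 gives 18.5, so 19 per arm. Using 10% therefore raises the sample from 19 to 26.

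**The case against.** Four objections deserve an answer.

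*The sentence gives no size for the placebo effect, and modest excesses can still be significant.* With 15/30 active and 7/30 sham successes, z = 0.267/√(0.367 × 0.633 × 2/30) = 2.14, p = 0.032. With 18/36 and 9/36, z = 0.25/√(0.375 × 0.625 × 2/36) = 2.19, p = 0.028. So an observed sham rate of 23–25% need not remove significance if the active arm reaches 50%. This is correct, but it describes particular observed results. The probability of obtaining such results is the power, and at true rates of 50% and 25% that is 52% with 30 per arm and 59% with 36.

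*Placebo response, natural recovery and the booklet act in both arms.* The article does give the booklet to every enrolled participant, and step 4 shows that an equal lift would keep power close to target. This makes the loss of power conditional. It does not rescue the sentence, because the article fixes active success at 50% and attributes the placebo effect to the sham device, without arguing for a parallel rise.

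*5% is not the only value the premise allows.* If a fraction b of patients would succeed without any device effect, then P2 = b + 0.1(50% − b), which reaches 10% at b of about 5.6%. The article gives no such baseline, so the fair criticism is that the derivation is not shown. A reader might infer that 10% is wrong and the trial wrongly sized. The text does not force that, and the discrepancy is conservative.

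*The calculation concerns binary success, whereas the primary outcome is described as RMDQ scores at T4.* This stands as a limit: the figures above do not give the power of a comparison of scores. The robustness sentence, however, is about the difference in success rates, and is tested here on those terms.

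**Conclusion.** The robustness statement is unsupported by the calculation it accompanies and should not stand. With active success at 50% and a two-sided 5% test, the stated 90% power holds only for sham success up to about 12.5% (30 completers per arm) or 15% (all 36 analysed). At an assumed 20% it is already 69% or 77%.

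Stronger readings are not supported. A reader might infer that the trial has 35% power. That figure needs a 30% sham rate, which is an illustrative assumption and appears nowhere in the article. A reader might also infer that the RMDQ comparison is underpowered, or that a null result will be taken as proof of no effect; the article supports neither. The unexplained step to 10% is a gap in reasoning that does no harm to the sample size.

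**What to change.** In the Sample size calculation section:

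1. Delete the sentence claiming robustness to an unexpected placebo effect.
2. State instead that, with active success at 50%, 90% power holds only for sham success up to about 12–15%, depending on how many of the 36 per arm complete.
3. Print power for sham success of 10%, 20%, 30% and 40% at 30 and 36 per arm, with the sham rates labelled as assumptions and the sidedness of the test given.
4. Present the 10% sham rate as an assumption and not as a consequence of the device's inhibited output.

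The cost is a few sentences and a four-row table. No patients are added, and no outcome or analysis changes. The drawback is that the stated power will look less favourable.
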